## Abstract

**Introduction:**

Malignant pleural effusion (MPE) is common, with 50 000 new cases per year in the UK. MPE causes disabling breathlessness and indicates advanced disease with a poor prognosis. Treatment approaches focus on symptom relief and optimising quality of life (QoL). Patients who newly present with MPE commonly require procedural intervention for both diagnosis and therapeutic benefit.

Thoracoscopic pleural biopsies are highly sensitive in diagnosing pleural malignancy. Talc poudrage may be delivered at thoracoscopy (TTP) to prevent effusion recurrence by effecting pleurodesis. Indwelling pleural catheters (IPCs) offer an alternative strategy for fluid control, enabling outpatient management and are often used as ‘rescue’ therapy following pleurodesis failure or in cases of ‘trapped lung’. It is unknown whether combining a TTP with IPC insertion will improve patient symptoms or reduce time spent in the hospital.

The randomised thoracoscopic talc poudrage + indwelling pleural catheters versus thoracoscopic talc poudrage only in malignant pleural effusion trial (TACTIC) is the first randomised controlled trial (RCT) to examine the benefit of a combined TTP and IPC procedure, evaluating cost-effectiveness and patient-centred outcomes such as symptoms and QoL. The study remains in active recruitment and has the potential to radically transform the pathway for all patients presenting with MPE.

**Methods and analysis:**

TACTIC is an unblinded, multicentre, RCT comparing the combination of TTP with an IPC to TTP alone. Co-primary outcomes are time spent in the hospital and mean breathlessness score over 4 weeks postprocedure. The study will recruit 124 patients and aims to define the optimal pathway for patients presenting with symptomatic MPE.

**Ethics and dissemination:**

TACTIC is sponsored by North Bristol NHS Trust and has been granted ethical approval by the London-Brent Research Ethics Committee (REC ref: 21/LO/0495). Publication of results in a peer-reviewed journal and conference presentations are anticipated.

**Trial registration:**

ISRCTN 11058680.

WHAT IS ALREADY KNOWN ON THIS TOPICDefinitive pleural intervention is advised to achieve symptom control in malignant pleural effusion (MPE). This may take the form of talc pleurodesis, which typically necessitates an inpatient admission of up to 7 days, or by inserting an indwelling pleural catheter (IPC). Two observational series have examined thoracoscopic talc pleurodesis (TTP) and IPC as a combined procedure, suggesting high pleurodesis rates, outpatient management and no safety concerns.WHAT THIS STUDY ADDSNo randomised controlled trial (RCT) has yet compared a combined TTP and IPC procedure early in the patient pathway against standard care (TTP), using validated patient-reported outcome measures. TACTIC is the first trial to robustly challenge the hypothesis that TTP with IPC insertion offers effective pleurodesis at the time of diagnostic biopsy with complete outpatient management, evaluating outcomes that are highly important to patients such as symptoms and quality of life.HOW THIS STUDY MIGHT AFFECT RESEARCH, PRACTICE OR POLICYThe TACTIC trial is a multicentre RCT with the potential to radically affect how patients with MPE are treated. By streamlining both diagnostic and therapeutic pathways into a single ambulatory procedure, a positive trial outcome is likely to result in this approach being widely adopted by healthcare systems.

## Introduction

Malignant pleural effusion (MPE) occurs when cancer metastasises to the pleura (most commonly from lung cancer in men and breast cancer in women) or in mesothelioma, when the pleura itself is the primary site of malignancy.^1 2^ It is common, with 50 000 new cases per year in the UK^3^ and incidence is likely to rise as global cancer rates increase.^4^ MPE causes disabling breathlessness and indicates advanced disease, with a median survival of 3–12 months.^1^ Treatment focuses on symptom control and optimising quality of life (QoL).

For most patients who newly present with a potential MPE, there is both a diagnostic and therapeutic need. An initial thoracocentesis to obtain pleural fluid (PF) for analysis and to relieve breathlessness is the first step in the standard care pathway, with cytology diagnostic in 46% (95% CI 42% to 58%).^5^ When MPE is suspected but PF is non-diagnostic, pleural biopsies are required and obtained via thoracoscopy or image guided techniques. Diagnostic sensitivity of biopsies obtained at medical thoracoscopy is >93%.^6^

The majority of patients will experience fluid re-accumulation following initial drainage, with associated symptom recurrence. Definitive intervention to provide long-term symptom relief is therefore advised.^1 4^ This may take the form of pleurodesis, a procedure where the lung is adhered to the chest wall using talc as a chemical sclerosant to prevent fluid recurrence. Talc may be delivered at thoracoscopy (‘talc poudrage’) or as talc ‘slurry’ by chest tube following fluid drainage, with no difference in pleurodesis efficacy between these methods (36/161 (22%) pleurodesis failures vs 38/159 (24%), respectively).^7^ While thoracoscopy and talc poudrage (TTP) allows the operator to offer pleurodesis in the same sitting as tissue biopsy (combining diagnosis and treatment in a single procedure) both TTP and talc slurry pleurodesis typically confer an inpatient hospital stay of up to 7 days.^8 9^ In addition to the resource pressures of modern-day healthcare systems, elective hospital admission in the context of poor estimated survival may be unacceptable to the patient for a variety of reasons.

Indwelling pleural catheters (IPCs) are an alternative method for definitive fluid management, offering comparable breathlessness control to talc pleurodesis and improved QoL.^10^ IPCs are tunnelled catheters, which are inserted as a day-case procedure and can remain in situ long term, allowing PF drainage to be conducted at home. They can be used where pleurodesis has failed and are also an option for patients who have ‘trapped lung’ (where the lung is unable to expand when fluid is drained), which occurs in 15% of patients with MPE.^1 8^

### Rationale for the study

The current standard care patient pathway and protocol for the randomised thoracoscopic talc poudrage + indwelling pleural catheters versus thoracoscopic talc poudrage only in malignant pleural effusion trial (TACTIC) are highlighted in figure 1.

**Figure 1 F1:**
[figure not shown]
Comparison of standard care patient pathway and TACTIC protocol. IPC, indwelling pleural catheter.

A procedure combining medical thoracoscopy, talc poudrage and IPC insertion (TTP and IPC) may overcome the usual requirements for an inpatient admission following talc pleurodesis. A combined procedure can mitigate the risk of pleurodesis failure following TTP (including as a result of ‘trapped lung’), as patients can continue to drain their effusion using the IPC and effectively control their symptoms without the need for further invasive interventions. TTP with IPC insertion may therefore also provide more effective symptom control, better QoL and cost savings to the healthcare system.

Two observational series have examined TTP and IPC insertion as a combined procedure, suggesting high pleurodesis rates (92%) at 1 month, median time to IPC removal of <14 days, no significant safety concerns and the ability to deliver the procedure in the outpatient setting.^11 12^ However, these studies were uncontrolled and did not assess QoL or patient reported symptoms. No randomised controlled trial (RCT) has yet compared a combined TTP and IPC procedure early in the patient pathway against standard care (TTP) using patient-reported outcome measures validated for use in the MPE population^13^ and qualitative methods to evaluate and characterise the impact of this intervention on patients and carers.

## Methods and analysis

TACTIC is a non-commercial, multicentre RCT based in UK secondary and tertiary care hospitals. Patients will be recruited from 10 centres with established thoracoscopy and IPC services. A list of participating sites can be found in online supplemental appendix E.

10.1136/bmjresp-2023-001682.supp1Supplementary data

### Population

We aim to recruit 124 participants with symptomatic MPE, who will be undergoing TTP for effusion control. Both patients in whom MPE is suspected, but not yet confirmed, as well as those with a confirmed diagnosis of MPE are eligible. Participants will be identified by clinicians working in pleural services in the selected centres only, from any part of the pleural service (inpatient, outpatient and procedure lists). They will be screened using the inclusion and exclusion criteria:

Inclusion criteria:

Symptomatic pleural effusion and any of the following:Thoracoscopically confirmed evidence of malignant pleural disease (visible cancer at thoracoscopy) which requires talc poudrage as part of routine clinical care.An established diagnosis of MPE (via biopsy or cytology) which requires drainage and pleurodesis as per standard care, where the patient and operator decide on a thoracoscopic treatment.Symptomatic effusion requiring drainage and pleurodesis in the context of established metastatic disease.Able to consent to trial inclusion.

Exclusion criteria:

Technically unable to undergo TTP (eg, gross respiratory failure, uncorrectable clotting, unable to tolerate position, significant suspicion of underlying trapped lung or poor performance status).Visual impairment (precluding use of symptom measurement instruments).Previous talc pleurodesis within the last 3 months on ipsilateral side.No means of phone contact.Age <18 years.Females who are pregnant or lactating.Unable to consent to trial inclusion.

Radiological confirmation of a pleural effusion with a chest X-ray (CXR) or thoracic ultrasound (USS) within 2 weeks of the screening consultation is required. In all cases, USS should be performed before randomisation to ensure there is sufficient fluid to conduct a thoracoscopy.

### Consent and randomisation

Participation in the trial will be discussed with the patient at the appropriate consultation, which will form part of their normal care pathway. Written informed consent will be received. Patients with suspected malignancy who are undergoing thoracoscopy for both diagnosis and symptom control will be advised that if pleural appearances during the procedure are not consistent with frank cancerous change, they will not be randomised and will not therefore continue with trial participation. Participants will be informed that they have a right to withdraw from the trial at any time, without having to give a reason and that this will not affect their future care.

Patients will be randomised on a 1:1 basis to receive the trial procedure (TTP+IPC) or standard care (TTP alone) using a web-based randomisation system. Patients with an established diagnosis of MPE may be randomised on the day of their procedure, or up to 48 hours in advance. Where a diagnosis of MPE is not established but findings at thoracoscopy are consistent with malignant disease, randomisation will occur during the procedure. Only patients with findings at thoracoscopy consistent with frank malignant change will be randomised. Patients will not be entered into the trial if there is diagnostic doubt.

Blinding for this study is not feasible given that the TTP+IPC arm will be discharged with an IPC in place.

### Intervention

Trial interventions are summarised by figure 2 and in the schedule of study procedures in online supplemental appendix A.

**Figure 2 F2:**
[figure not shown]
Trial flow chart. CRF, case report form; CXR, chest X-ray; LAT, local anaesthetic thoracsocopy; MPE, malignant pleural effusion; QoL, quality of life; US, ultrasound; VAS, visual analogue scale; WHO PS, World Health Organisation Performance Status.

All patients will undergo a TTP. Those randomised to the intervention arm will have an IPC inserted in addition. TACTIC will provide sites with IPCs (Rocket medical) but sites may choose to use alternative equivalent devices. If talc poudrage at time of thoracoscopy is not possible, for example, due to patient discomfort, it is possible for patients to proceed within the trial if talc slurry is administered within 24 hours of the thoracoscopy. These patients should continue to receive their allocated treatment (IPC or standard care). If patients in either arm do not receive either a talc poudrage or talc slurry (within 24 hours), this would be considered a treatment failure. If an IPC is not sited for patients in the intervention arm, this would also be considered a treatment failure. In cases of treatment failure, clinical care should continue as per usual practice, a protocol deviation should be completed with the appropriate case report form (CRF) and patients should continue with trial follow-up and assessments.

Medical thoracoscopy will be performed according to local practice, but consistent with the British Thoracic Society guideline.^6^ Specific to TACTIC participation, sites are advised to insert the IPC prior to talc poudrage (if the patient is allocated to the intervention arm) to avoid potential difficulty placing the IPC if the patient experiences discomfort post-poudrage. It is advised that the IPC should be inserted through a separate entry to the thoracoscopy port and all patients should have a large bore drain (16–24 Fr) inserted via the port site. Talc poudrage or slurry should be administered with 3–4 g sterile graded talc.

TTP participants will be admitted to hospital postprocedure as per standard care and discharged at the discretion of the treating clinician. TTP+IPC participants will be assessed for discharge on the same day as the intervention but may be admitted if clinically required. For patients who remain an inpatient the trial team will record the day on which suggested discharge criteria (outlined in a trial specific procedure) were met and the day on which discharge occurred.

For intervention arm participants, IPC drainages will be performed by a trained healthcare professional, a minimum of 5 times per week until the first clinic review at 14 days. Participants will be advised to report to the local trial team if PF drains <50 mL on three consecutive drainages. Following this, a clinical review within 7 days will be arranged to consider repeat imaging and IPC removal, which should take place any time up to 14 days after this point. Any patient who has their IPC removed will continue to undergo planned follow-up for the full 12 weeks.

All participants will be given patient diaries to capture visual analogue scale (VAS) scores for breathlessness and chest pain, recorded two times a week over 4 weeks post procedure. Diaries will also capture interaction with healthcare providers. Participants randomised to the intervention arm will record IPC drainage volumes. An extract of the patient diary is included in online supplemental appendix B.

All concomitant medications (other than other intrapleural pleurodesis agents) are permitted in this trial. Use of medications which are thought to reduce pleurodesis success (such as steroids) are permitted but will be recorded on CRFs. There are no trial restrictions, and participants can take part in other (non-pleural interventional) studies if the other trial protocols permit this. Participants in the non-IPC arm are permitted use of IPCs during the post pleurodesis phase if PF becomes recurrent, and this will be recorded on the CRFs. All other forms of pleurodesis (including via the IPC if present) are not permitted during the first month of follow-up.

### Follow-up visits

Participants will be followed up for 12 weeks after the trial procedure, or until death. Trial visits will take place at 2 weeks±3 days, 4 weeks±3 days and 12 weeks±7 days post procedure. At each visit, participants will undergo a standard clinical assessment, including CXR and thoracic USS. QoL questionnaires (EuroQol 5-Dimension 5-Level(EQ5D-5L) and European Organisation for Research and Treatment of Cancer Quality of Life of cancer patients (EORTC QLQc30) will be completed at 4 weeks and 12 weeks. Adverse events (AEs) will also be recorded. Loss to follow-up will be minimised by diligent liaison with the patient, their oncology team and general practitioner. Any loss to follow-up will be recorded on the withdrawal CRF. The reason for withdrawal (if known) will be recorded.

### Carer questionnaires

As an optional aspect of the trial, primary care givers will be asked to complete questionnaires to capture the impact of informal care giving. These will include the Short Form -36 (SF-36); a 5-item scale capturing physical, financial, emotional, social and overall impacts of care burden and the Work Productivity and Activity Impairment as adapted for caregiving (WPAI (CG)) which will ask about productivity losses. Questionnaires will be answered at baseline, 4 weeks and 12 weeks following the patient’s trial procedure.

### Qualitative interview

Patients and their carers (spouse, family or friend) will be invited to participate in a qualitative interview to explore the patient experience of the trial procedures, to characterise the impact of treatment on patient and carer, management of the condition, well-being and QoL. Interviews will be conducted between 4 and 12 weeks (+1 week) following the trial intervention. Patients and carers may be approached about participating in a qualitative interview at any time during the trial period.

### Study outcomes

Our primary research question is:

‘In symptomatic patients with suspected or established MPE, does a combined TTP and IPC result in a reduction in time in hospital and an improvement in dyspnoea, when compared with TTP alone?’

Two co-primary outcomes were chosen to reflect patient priorities in the treatment of MPE, based on patient and public involvement (PPI) feedback. Specifically, these co-primary outcomes will measure total length of stay in hospital (including re-admissions) and average breathlessness scores over 4 weeks postprocedure.

Time spent in hospital will be calculated in whole days, with an overnight admission or continuous period in hospital of >12 hours constituting 1 day. Mean breathlessness scores will be assessed using a 100 mm VAS for dyspnoea. This is validated in patients with MPE undergoing pleural aspiration and has a defined minimal clinically significant difference. VAS dyspnoea scores will be collected at baseline, day 1 postprocedure, day 5 postprocedure and then two times a week for 4 weeks.

Our secondary outcomes are:

Effect of TTP+IPC on chest pain over 4 weeks, measured two times a week using a 100 mm VAS score for pain.Total length of stay in hospital over 12 weeks post procedure.Total length of stay in hospital over 4 weeks post procedure, once time spent in hospital for non-medical reasons is discounted. Assessed as total number of days until medically appropriate for discharge according to criteria specified in a trial specific procedure.Pleurodesis success, measured at 4 and 12 weeks post procedure. Defined as absence of a pleural effusion of at least moderate size radiologically (greater than or equal to one-third of hemithorax on CXR or >2 rib spaces and 4 cm depth on ultrasound) AND no further requirement for pleural procedures for effusion control, OR for TTP+IPC participants an IPC output of <50 mL on three consecutive drainages.Healthcare contacts over 12 weeks post procedure, captured using questionnaires and patient diaries.QoL measured using the EQ5D-5L and EORTC QLQc30 questionnaires at baseline, 4 and 12 weeks post procedure.Cost effectiveness of the interventions.Caregiver burden captured using SF-36, WPAI (CG) and 5 item scale questionnaires to capture informal caregiving, measured at baseline, 4 and 12 weeks.Patient and carer experiences of TTP+IPC compared with TTP alone, captured by semistructured qualitative interviews.

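### Pleurodesis success: the output criterion open only to TTP+IPC has no re-treatment condition and no time anchor, so a re-treated patient can count as a success in that arm but never in the TTP arm

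*Protocol article*

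**What the plan says.** Under Study outcomes, pleurodesis success is assessed at 4 and 12 weeks. The first route is open to both arms and joins two conditions with AND: imaging shows no effusion of at least moderate size, and there is "no further requirement for pleural procedures for effusion control". The second route follows: "OR for TTP+IPC participants an IPC output of <50 mL on three consecutive drainages".

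The Intervention section supplies the context:
- Three low-output drainages prompt a clinical review that considers removing the IPC. Follow-up continues to 12 weeks after removal.
- TTP-alone participants may receive an IPC if fluid recurs.
- On repeat pleurodesis, one sentence reads "All other forms of pleurodesis (including via the IPC if present) are not permitted during the first month of follow-up". Another, with no time limit, reads "All concomitant medications (other than other intrapleural pleurodesis agents) are permitted in this trial".

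The Rationale describes the expected course after failed pleurodesis in the combined arm as one in which "patients can continue to drain their effusion using the IPC and effectively control their symptoms without the need for further invasive interventions".

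**The concern.** The condition on further procedures binds the TTP arm in every case. In the TTP+IPC arm it binds only those who do not meet the output criterion. The same clinical event, recurrence that needs another procedure, can therefore be scored failure in one arm and success in the other.

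Two courses lead there:
1. **Recurrence after removal.** A participant meets the output rule early, has the IPC removed, re-accumulates fluid and needs a new drainage procedure. The rule does not say when the three drainages must fall relative to the assessment, so the earlier low output can still be read as qualifying.
2. **Second pleurodesis after month 1.** A participant fails the index pleurodesis, receives a further agent in weeks 5 to 12 and then drains little.

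At stake is the between-arm comparison of pleurodesis success, in an unblinded trial, with the error running towards TTP+IPC. The first course could affect either assessment; the second could affect only the 12-week one.

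**Working it through.** **Step 1: the logic.** Let A = no moderate effusion on imaging, B = no further procedure required, C = low output on three drainages. As written, TTP success = A and B; TTP+IPC success = (A and B) or C. The cases in which B fails are:

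| A | B | C | TTP | TTP+IPC, (A and B) or C | TTP+IPC, A and (B or C) | B and (A or C) |
|---|---|---|---|---|---|---|
| no | no | no | fail | fail | fail | fail |
| no | no | yes | fail | **success** | fail | fail |
| yes | no | no | fail | fail | fail | fail |
| yes | no | yes | fail | **success** | **success** | fail |

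Both groupings that the word order allows let C stand in for B. Only B and (A or C) scores every re-treated patient as a failure, and the sentence does not read that way.

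**Step 2: size.** The article gives no planned figure for this outcome to reproduce, and no rate of re-treatment, so what follows is an illustration.

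*Evaluable per arm at 12 weeks.* 124/2 = 62, less 5% loss: 62 × 0.95 = 58.9. The Introduction gives "median survival of 3–12 months". Assuming exponential survival and deaths not scored, 12 weeks is about 2.76 months:
- median 3 months: 0.5^(2.76/3) = 0.529; 58.9 × 0.529 ≈ 31
- median 12 months: 0.5^(2.76/12) = 0.853; 58.9 × 0.853 ≈ 50

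*Failure rate f.* 8%, from the uncontrolled combined-procedure series ("suggesting high pleurodesis rates (92%) at 1 month"). As an upper case, 23%, from the talc trial figures ("36/161 (22%) pleurodesis failures vs 38/159 (24%), respectively"): 74/320 = 23.1%.

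*Share q.* The proportion of TTP+IPC failures that the output route turns into successes despite a further procedure. Assumed to be 10%, 25% or 50%; no source in the document.

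Shift in TTP+IPC success = f × q; patients rescored = n × f × q.

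| f | q | Shift (points) | Patients, n = 31 to 50 |
|---|---|---|---|
| 8% | 10% | 0.8 | 0.2 to 0.4 |
| 8% | 25% | 2.0 | 0.6 to 1.0 |
| 8% | 50% | 4.0 | 1.2 to 2.0 |
| 23% | 10% | 2.3 | 0.7 to 1.2 |
| 23% | 25% | 5.8 | 1.8 to 2.9 |
| 23% | 50% | 11.5 | 3.6 to 5.8 |

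*Chance of a significant difference when true success is equal.* Exact two-sided Fisher test at 5%, with success 1 − f in TTP and 1 − f + fq in TTP+IPC:

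| f | n per arm | q = 0 | 10% | 25% | 50% |
|---|---|---|---|---|---|
| 8% | 31 | 0.006 | 0.006 | 0.007 | 0.011 |
| 8% | 50 | 0.015 | 0.015 | 0.019 | 0.041 |
| 23% | 31 | 0.025 | 0.028 | 0.046 | 0.131 |
| 23% | 50 | 0.030 | 0.035 | 0.071 | 0.241 |

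At 8% failure the probability stays below the nominal 5% throughout. It passes 5% only at 23% failure, with q = 25% and 50 per arm, or with q = 50%.

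**The case against.** **An arm-specific criterion has a purpose.** TTP+IPC participants are drained at least five times a week until day 14, so a condition about further procedures is awkward while a trial catheter is in use, and low output is the trial's own prompt for removal. This stands: the output criterion itself is reasonable. What is not needed is the exemption from re-treatment that comes with it.

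**Second pleurodesis is not a planned treatment.** A reader might infer from the month-1 ban that the protocol allows re-treatment from week 5. The documents do not support that. The sentence on concomitant medication excludes other pleurodesis agents without a time limit, and the Rationale expects continued IPC drainage. Weeks 5 to 12 are ambiguous, not clearly open. The event could still occur, permitted or as a deviation, and would then need scoring.

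**Assessment at 4 and 12 weeks implies current output.** On that reading a removed catheter has no output, and the course of recurrence after removal closes. The definition does not say so, however, and a second pleurodesis with the IPC still in place would remain.

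**The full protocol or the SAP may settle it.** The article condenses protocol V6.0 and places the SAP in an appendix that is not shown. This lowers confidence. It does not remove the point, because the AND/OR rule is stated text and treats the arms differently as stated.

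**Conclusion.** The point holds as a minor fault in one secondary outcome. As written, the definition can score a re-treated TTP+IPC participant as a success, while a re-treated TTP participant always fails. The direction favours TTP+IPC.

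The size is unknown and probably small. It rests on assumed shares, on borrowed failure rates, and on exponential survival with deaths unscored. At the only failure rate that the document gives for the combined procedure, the effect on the comparison is negligible for shares of 10% to 25%.

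Two stronger conclusions should not be drawn. A reader might take the 0.241 in the table as the expected false-positive rate; it combines the highest failure rate, the highest share and the longest survival. A reader might also think that the trial's main result is biased. Time in hospital and mean breathlessness do not use this definition, and neither does the sample size.

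**What to change.** Add one sentence to the definition under Study outcomes, for example: *Any second pleurodesis by any route, or any new pleural procedure for recurrent effusion, before an assessment counts as pleurodesis failure at that assessment in both arms and overrides the IPC-output criterion. Routine drainage through the trial IPC, its removal, and its replacement or unblocking for a mechanical fault do not count.* The last exemption matters: without it, replacing a blocked or displaced trial IPC would count as failure almost only in the TTP+IPC arm and create the opposite imbalance.

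Also align the two sentences in the Intervention section so that they give one duration for the bar on other pleurodesis agents, and record the date of each further procedure if the CRF does not already do so.

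The cost is some wording and possibly one date field; treatment, visits and sample size do not change. The downside is slightly lower pleurodesis success in the TTP+IPC arm. If the full protocol or SAP already contains this rule, only the published definition needs aligning.
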